### Objectives

The objectives of this randomized controlled trial are:

To investigate any add-on benefit of oral Chinese herbal medicine (YXBCM01) to calcipotriol for the management of psoriasis vulgaris;To investigate whether combination of oral Chinese herbal medicine (YXBCM01) and calcipotriol is safe for the management of psoriasis vulgaris.

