### Sample size determination

A pilot study of 30 participants testing the feasibility of the trial protocol will be conducted prior to a full scale trial. Post-hoc power analysis via effect size estimation on the pilot study data will be used to determine sample size for a full scale trial.

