### Randomization, sequence generation and allocation concealment

Participants will be randomly allocated to intervention (YXBCM01 plus calcipotriol) or control group (placebo plus calcipotriol) in equal ratio (1:1). Randomization numbers will be computer generated in blocks and corresponding codes sealed in opaque envelopes. Envelopes will be opened sequentially from each block only after the participant’s details are written on the outside of the envelope. The code inside the envelope will correspond to a package number that will contain 12 weeks supply of either YXBCM01 granules or identically packaged placebo granules.

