### Statistical analysis methods

All data will be analyzed by an independent statistician. The Statistical Package for the Social Sciences software version 21.0 for Windows (SPSS Inc., Armonk, New York, USA) will be used for data analysis. Baseline demographic characteristics on categorical variables, such as sex, will be assessed for balance between the two treatment groups via the chi square test, whilst continuous or interval variables will be assessed for equivalence between the treatment groups by *t* tests. Intention-to-treat analysis will be applied to outcome data to minimize bias due to withdrawals; all missing data will be replaced using the last observation carried forward. Continuous data will be presented as means and standard deviation, or 95% confidence interval. All dichotomous data, such as the percentage of participants achieving PASI 75, will be presented as risk ratio and 95% confidence interval. Other outcomes (for example, severity and quality of life) will be assessed for equivalence in the two groups; *P* < 0.05 obtained from statistical tests on variables involving treatment group comparisons will be considered statistically significant.

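### The analysis section frames outcome comparisons as equivalence, with a P < 0.05 criterion and no margin, although the objective is add-on benefit

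*Protocol article*

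**What the plan says.** Under Objectives, the efficacy aim is "To investigate any add-on benefit of oral Chinese herbal medicine (YXBCM01) to calcipotriol for the management of psoriasis vulgaris". The comparator is placebo plus calcipotriol.

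Under Statistical analysis methods, three statements bear on group comparisons:

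- For outcomes: "Other outcomes (for example, severity and quality of life) will be assessed for equivalence in the two groups". The same sentence continues, after a semicolon, that P < "0.05 obtained from statistical tests on variables involving treatment group comparisons will be considered statistically significant".
- For continuous baseline data: "continuous or interval variables will be assessed for equivalence between the treatment groups by" *t* tests.
- For categorical baseline data, the variables "will be assessed for balance between the two treatment groups via the chi square test". Here the word is balance, not equivalence.

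The article gives no equivalence margin and no equivalence procedure. It names no test for the other outcomes. Under Sample size determination it states: "A pilot study of 30 participants testing the feasibility of the trial protocol will be conducted prior to a full scale trial". Allocation is 1:1.

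**The concern.** Add-on benefit asks whether the herbal arm does better than the placebo arm. Equivalence is the opposite claim: if it were shown, the herbal medicine would add nothing of consequence. The two need different hypotheses and different procedures. An equivalence claim needs a margin fixed in advance and a test against that margin. A P value below 0.05 from a test of difference is evidence of a difference, and a P value above 0.05 is not evidence of equivalence.

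For continuous outcomes, the equivalence sentence is the only one in the section that says what the between-group comparison is for; the rest says how data are presented. An analysis plan or report that followed it could describe a non-significant comparison as showing equivalent groups. In a trial this small, such a result is compatible with a large real benefit.

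The same wording is applied to continuous baseline variables. That is a lesser matter. After sound randomization, baseline differences are due to chance, and non-significance with 15 per arm does not show that the groups are comparable.

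**Working it through.** **Comparing the sections.** The Objectives section asks about benefit over calcipotriol. The opening of Methods/design likewise seeks an indication of efficacy against calcipotriol plus placebo. Statistical analysis methods states an equivalence aim for severity and quality of life. These do not agree, and seeing that needs no outside figure.

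**Is there a figure to reproduce?** No. The article states no power, effect size, SD or margin. What follows is illustration on assumed standardized values.

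**Inputs from the protocol.** 30 participants (Sample size determination), allocated 1:1 (Randomization section), so 30/2 = 15 per arm and 15 + 15 − 2 = 28 degrees of freedom. Significance level 0.05 (Statistical analysis methods).

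**Assumptions.** Two-sided testing, because sidedness is not stated; a two-sample *t* test, because no test is named for these outcomes; no dropout; true differences and margins in SD units, shown as a range.

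**Step 1: precision.** The standard error of a difference in means is SD × √(2/15) = 0.365 SD. The 95% CI half-width is t(0.975; 28) × 0.365 = 2.048 × 0.365 = 0.75 SD.

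**Step 2: chance that a real difference is non-significant.** The noncentrality parameter is d × √(15/2) = 2.739 d. Power comes from the noncentral *t* distribution with 28 df.

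| Assumed true difference (SD) | Noncentrality | Power | Non-significant |
|---|---|---|---|
| 0.2 | 0.55 | 8% | 92% |
| 0.5 | 1.37 | 26% | 74% |
| 0.8 | 2.19 | 56% | 44% |
| 1.0 | 2.74 | 75% | 25% |

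A power of 80% needs a true difference of about 1.06 SD.

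**Step 3: if equivalence were really intended.** Two one-sided tests at 5% each correspond to a 90% CI lying wholly inside the margin. Its half-width is about 0.62 SD. Power at a true difference of zero was found by simulation (400,000 replicates, 15 per arm). The number per arm for 80% power is approximately 2 × ((1.645 + 1.282)/margin)².

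| Assumed margin (SD) | Power at 15 per arm | Needed per arm for 80% |
|---|---|---|
| 0.5 | 0.5% | 69 |
| 0.8 | 38% | 27 |
| 1.0 | 69% | 18 |

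At 2.5% per side the three powers fall to about 0%, 16% and 51%.

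**Reading the results.** A non-significant result would be common even with differences of 0.5 to 0.8 SD, so it cannot support equivalence. A proper equivalence test would be nearly hopeless at a 0.5 SD margin, and it would still fall short of 80% power at a margin as wide as 1.0 SD.

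**The case against.** The strongest reply is that equivalence is loose language for comparing the groups. The design is a placebo-controlled add-on comparison, the P < 0.05 rule belongs to a test of difference, and the baseline sentence sets balance beside equivalence as if they were interchangeable. This is plausible. If it is right, correcting the word is enough, but the word still has to be corrected, because as printed it names a hypothesis the trial does not pose.

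Several stronger readings are tempting, and the document does not support them:

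- *That non-significance will be reported as equivalence.* No sentence says so. It is an inference from pairing the word with P < 0.05 and no margin.
- *That the outcomes will be analysed with* t *or chi-square tests.* Those are named only for baseline variables. The choice of outcome test may sit in an analysis plan that is not shown, and its absence here is no fault.
- *That P > 0.05 is the most likely result.* This depends on the unknown true effect. At 0.8 SD, significance is the more likely result (56%).
- *That baseline testing will distort the analysis.* No covariate choice, exclusion or other decision is tied to those tests. The number of tests is not given, and the baseline severity and quality-of-life measures are unlikely to be independent, so no overall false-positive rate can be put on them.
- *That the sample size is wrong.* The 30 is a feasibility number, and the full trial is to be sized from an estimated effect, not from a P value or an equivalence finding.

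Part of the remedy is also already present: risk ratios with 95% CIs are planned for dichotomous outcomes, and continuous data may be given with a 95% CI.

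**Conclusion.** The concern holds as a conflict between the stated analysis aim and the stated objective. It is established by the text alone: equivalence wording for severity and quality-of-life outcomes, a P < 0.05 criterion, no margin, and an add-on-benefit objective. The article does not settle whether *severity* includes the primary PASI outcome, so the reach of the sentence is uncertain.

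The calculations show why the wording matters at 15 per arm, but they rest on assumed effects, margins, sidedness and test. They are not estimates for this trial.

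Because this is a feasibility pilot and no decision is tied to the equivalence phrase, the consequence is confined to misleading interpretation of the comparisons. It should be corrected, but it does not undermine the design. Baseline testing is a secondary point of good practice.

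**What to change.** In Statistical analysis methods:

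1. For outcomes, replace the equivalence wording with a statement that outcomes will be compared between groups as the baseline-adjusted difference with its 95% CI. Where no baseline value exists, as for acceptability, give the unadjusted comparison.
2. Add that P ≥ 0.05 will not be interpreted as equivalence or as absence of effect.
3. As a secondary change, replace the *t* tests for equivalence and the chi-square tests for balance at baseline with a descriptive table by group.

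If equivalence is truly intended for any outcome, the protocol would have to name that outcome, justify a margin and specify a test against it, with the limits of 15 per arm acknowledged.

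The cost is wording only. Baseline PASI, body surface area, Dermatology Life Quality Index and Skindex 29 are already collected at visit 2 (Table 1), so no new data or visits are needed. The change should be made and dated before the randomization codes are broken.

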## Discussion

### Outcome measures used in this study

From research, complete clearance of psoriasis symptoms is rarely achievable; as a result, treatment success is based on reduction in PASI of 75% (PASI 75) [44]. Treatment failure is regarded as a reduction in PASI of less than 50% (PASI 50). For those PASI changes falling between this range (≥50% but <75%), the Dermatology Life Quality Index is used to determine whether current treatment should be modified or continue [45]. The Therapeutic Goods Administration recommends standard outcomes of PASI 75, PASI 50 and body surface area to assess product efficacy for psoriasis [44]. The Dermatology Life Quality Index is recommended by both the Therapeutic Goods Administration and the Australian College of Dermatologists, to evaluate psoriasis severity and patients’ quality of life [12, 44]. It is a validated instrument that is well-recognized in psoriasis research. The Skindex 29 has been evidenced for psoriasis as the most sensitive scale, with high applicability; previous evaluation identifies it as the most validated quality-of-life instrument for dermatological conditions [46, 47].

### Chinese medicine syndrome approach

As yet, there is no conclusive evidence that utilizing Chinese medicine syndrome theory in clinical trial treatment will improve the efficacy of treatment [48]. Whilst this study will not allocate treatment based on syndrome differentiation, it will be able to analyze the results of the intervention and investigate whether there are differences in efficacy between participants in each syndrome group (blood heat, blood dryness or blood stasis). With text books differing, there is conjecture about the number of Chinese medicine syndrome types for psoriasis; the development of the Chinese medicine syndrome differentiation criteria for this study was based on available Chinese guidelines, as well as expert consensus [23].

## Trial status

The trial is currently recruiting, following the protocol stipulated in the Australian and New Zealand Clinical Trials Registry.

## Abbreviations

PASI: Psoriasis Area Severity Index
PASI 50: reduction in PASI of less than 50%
PASI 75: reduction in PASI of 75%.
